#### Main outcome

The main outcome will be health-related quality of life measured with the Short Form-36 Health Survey (SF-36) [43, 44]. The SF-36 consists of 36 items that are scored on Likert-type scales from 1 to 3.5, or 6 depending on the specific item. It measures the following eight dimensions of health: physical function, physical role, aches and pains, general health, vitality, social function, emotional role, and mental health. In addition, the SF-36 incorporates a health progress item. For each dimension, the items are coded, aggregated, and transformed into a scale that ranges from 0 (the worst state of health for that dimension) to 100 (the best state of health). A score of 50 is typically considered the average or norm for the general population. The SF-36 general health (total) score will be considered the main outcome, and the SF-36 subscales described will be considered secondary outcomes. The Spanish version of the SF-36 has demonstrated good psychometric properties, establishing it as a reliable and valid tool for measuring health-related quality of life in the Spanish-speaking population. Internal consistency values for Cronbach’s alpha exceed 0.7 in all subscales as well as the total score [45].

#### Secondary outcomes

The intensity of chronic pain will be measured with the Spanish Chronic Pain Grading Scale (SCPGS) [46]. It comprises 10 items that are used to assess the intensity of pain at different times of the day, as well as its impact on the patient’s quality of life and daily functioning. Each item is scored on a scale from 0 to 10, where 0 means no pain, and 10 indicates the most intense pain imaginable. The total score ranges from 0 to 100, with a higher score indicating a greater intensity of chronic pain. The scale has been validated in Spanish patients with chronic pain and is considered a useful and reliable tool for the assessment of chronic pain in clinical practice and research (α = 0.87) [47].

Pain catastrophizing will be evaluated with the Pain Catastrophizing Scale (PCS) validated in Spanish [48]. This tool is a self-report questionnaire that measures catastrophized pain and consists of 13 items related to over-focusing on pain sensations, magnifying the threat value of pain sensations, and perceiving oneself as unable to control pain intensity. Items are rated in relation to their frequency of occurrence on a five-point scale, from never (0) to almost always [4]. The total PCS score is calculated as the algebraic sum of the scores for each item and ranges from 0 to 52, with higher scores reflecting a greater degree of pain catastrophizing. This version has adequate internal consistency (α = 0.79) and acceptable test-retest reliability (r = 0.84).

The Modified Fatigue Impact Scale (MFIS) is a multidimensional scale that has been used in numerous chronic pathologies [49]. It consists of 21 items distributed into three subscales: physical, cognitive, and psychosocial. Physical fatigue refers to the feeling of weakness and body exhaustion, accompanied by discomfort or even muscle pain and an inability to relax, which occurs after physical exertion; cognitive fatigue is a cognitive slowing or a feeling of dullness, which makes it difficult to perform tasks that require sustained mental effort; and psychosocial fatigue is the general feeling of exhaustion derived from carrying out social activities and outside the home. Each item is rated on a five-point Likert scale (from 0, “never,” to 4, “almost always”). The total score ranges from 0 to 84. A score of 38 has been established as a cut-off point to define the presence of fatigue. It assesses different aspects related to fatigue and cognitive and emotional affectation in a single form. It values physical and cognitive aspects, but is firmly focused on mental fatigue and its consequences, particularly the impact that fatigue has on the patient. The dimensions have shown adequate internal consistency (total score: α = 0.92; physical subscale: α = 0.88; cognitive subscale: α = 0.92, and psychosocial subscale: α = 0.65).

The Insomnia Severity Index (ISI) is a 7-item scale that assesses the symptoms of daytime and nocturnal insomnia and is widely used in the field of clinical research [50]. Each item is rated on a five-point Likert scale (e.g., 0 = no problem; 4 = very severe problem), yielding a total score ranging from 0 to 28. The information collected by this tool is related to the onset and maintenance of sleep, waking up in the morning, interference with daily functioning, deterioration perceived and attributed to the sleep problem, concerns about sleep problems, and satisfaction with sleep patterns. The validation of the Spanish version of the ISI has adequate internal consistency indices (Cronbach’s α = 0.82); it is significantly correlated with poor sleep quality, fatigue, anxiety, and depression; and it allows discrimination between people with good and bad sleep patterns [51].

Anxious symptomatology will be evaluated with the Generalized Anxiety Disorder-7 (GAD-7), which is made up of seven self-reported items [52]. Each item is scored on a four-point Likert scale (0 = “not at all”; 1 = “several days”; 2 = “more than half the days”; 3 = “nearly every day”), which results in a total score that can range from 0 to 21, with higher values reflecting more severe anxiety symptoms over the previous two weeks. Symptom severity can be organized into four categories: 0–4 (minimal anxiety), 5–9 (mild anxiety), 10–14 (moderate anxiety), and 15–21 (severe anxiety). The validation in Spanish has a sensitivity of 0.93 and a specificity of 0.85 [53].

The PHQ-9 is a nine-item self-report measure that assesses the presence of depressive symptoms based on the DSM-IV criteria for major depressive episode [54]. It refers to the symptoms experienced during the previous two weeks. The PHQ-9 is scored on a Likert scale (“never” = 0; “several days” = 1; “more than half the days” = 2; “almost every day” = 3), and the total score ranges from 0 to 27. Symptom severity can be organized into four categories: 0–4 (minimum), 5–9 (mild), 10–14 (moderate), 15–19 (moderate to severe), 20–27 (severe). The Spanish version of the scale will be used, which has demonstrated good psychometric properties (sensitivity = 87%; and specificity = 88%; Cronbach’s α = 0.835) [55].

The Memory Failures of Everyday Questionnaire (MFE) is one of the most widely used self-report questionnaires to assess daily forgetfulness [56]. Through 30 items and five response options (from 0 = “never” to 4 = “always”) memory failures and their frequency in daily life are evaluated. Several cut-off points are established: below 8 (optimal memory functioning), between 8 and 35 (normal functioning with memory lapses without influence on daily performance), between 36 and 50 (mnesic impairment with some impact on daily activity), and above 50 (moderate or severe memory impairment with greater impact on daily functioning). Studies have observed good internal consistency (α = 0.92).

#### Mechanistic measures

Mindfulness skills will be measured with a short version (24 items) of the Five Facet Mindfulness Questionnaire (FFMQ-24) [57]. This version is an adaptation of the original 39-item FFMQ, a questionnaire that measures the following five facets of mindfulness: observing (i.e., noticing internal and external experiences such as sensations, thoughts, or emotions), describing (i.e., labeling internal experiences with words), acting with awareness (i.e., focusing on one’s activities in the present moment as opposed to behaving automatically), nonjudging of inner experience (i.e., taking a nonevaluative stance toward thoughts and feelings), and nonreacting to inner experience (i.e., allowing thoughts and feelings to come and go, without getting caught up by them). Participants indicate the degree to which each of the items is generally true for them on a five-point Likert scale, from 1 (‘never or very rarely true’) to 5 (‘very often or always true’). Scores from the subscales can be summed to produce a total score that ranges between 24 and 120, with higher scores reflecting greater levels of mindfulness skills. The Spanish version of the short FFMQ-24 has good internal consistency values for the total score (α = 0.70), and subscales (α values ranging from 0.65 to 0.80) [58].

Emotional regulation capacity, which refers to an individual’s ability to modify the components of their emotional experience with respect to its frequency, form, duration, and intensity, will be measured with the Emotion Regulation Questionnaire (ERQ) [59]. This scale consists of 10 items, to which participants respond using a seven-point Likert scale (1 = “strongly disagree,” 7 = “strongly agree”). The ERQ is designed to measure the tendency of respondents to regulate their emotions through [1] cognitive reappraisal (6 items), and [2] expressive suppression (4 items). The cognitive reappraisal strategy modifies emotional reactions at the time of its gestation, managing to change the emotional experience. On the other hand, expressive suppression only modifies emotional expression and is an intentional hiding of the actual experience without altering it. The Spanish version of the ERQ shows adequate internal consistency (cognitive reappraisal: α = 0.89–0.90; expressive suppression: α = 0.76–0.80), test-retest reliability, and convergent/discriminant validity [60].

Experiential avoidance will be measured with the Acceptance and Action Questionnaire-II (AAQ-II) [61]. As opposed to psychological flexibility, experiential avoidance is a psychological construct associated with poorer mental health and reflects the tendency to avoid or escape from internal emotional experiences, thoughts, memories, sensations, or bodily sensations that individuals perceive as distressing, uncomfortable, or unwanted. It usually involves engaging in behaviors intended to distract or distance oneself from these experiences. It comprises seven items scored on a seven-point Likert scale, and whose total score is calculated by adding all the items. Higher scores mean greater experiential avoidance. The Spanish version of the AAQ-II presents good internal consistency (α = 0.84) and test-retest reliability (r = 0.79) [62].

## Data analysis plan

The distribution of the sociodemographic and clinical variables will be presented by frequencies (percentages), medians (interquartile range, IQR) or means (standard deviations, SD), according to their level of measurement and statistical distribution.

The primary analysis will consist of a comparison between AIR + Mindfulness (intervention arm) and relaxation therapy (control arm) at post-intervention, considering the quality-of-life main outcome (SF-36) as a continuous variable. It will be performed using a repeated measures design on an intention-to-treat (ITT) basis, and a linear mixed effects regression by means of the restricted maximum likelihood (RML) method, controlling for age and sex. The “treatment by time” interaction will be calculated to determine possible differences between the study arms over time. The slope coefficient, representing the adjusted mean difference change, as well as its 95% confidence interval (95% CI), will be calculated. Hedge’s g statistic, as an effect size measure of between-group differences, will be calculated from the raw data. The rule of thumb for effect size interpretation will be 0.20 = small, 0.50 = medium, and 0.80 = large.

Secondary analysis will explore the effects achieved in the primary outcome at three-month follow-up, as well as in the secondary outcomes at post-intervention and at three-month follow-up, following the same analytical approach. Sensitivity analysis will assess the effects of missing data, which will be assumed to be missing at random and replaced by multiple imputations based on chained equations, including the main and secondary outcomes of all the waves––as well as routinely collected sociodemographic data. Other secondary analyses will explore reliable change and clinically significant change in quality-of-life improvements using the Jacobson and Truax method [63]. These classifications will be used to calculate the absolute risk reduction (ARR) and the number needed to treat (NNT); a 95% CI for each NNT will also be calculated. We will use a two-sided test with a 0.05 significance level. No corrections for multiple comparisons will be made for the primary analysis––because only one contrast will be made. Secondary analyses will be corrected for multiple comparisons by adjusting the significance threshold according to the Benjamini-Hochberg procedure [64].

The potential role of mindfulness skills, emotion regulation, and experiential avoidance as potential mediators of improvements in both the primary and secondary outcomes will be explored. For this purpose, (a) pre-follow-up differential scores for primary and secondary outcomes will be considered dependent variables; (b) pre-post differential scores for mindfulness skills, emotion regulation, and experiential avoidance will be calculated and included as process variables; (c) the group condition (AIR + Mindfulness vs. relaxation therapy) will be considered the independent variable. The mediating analyses will be conducted using ordinary least squares (OLS) regression and path analysis for mediating analyses involving continuous dependent variables. Standardized regression coefficients of bootstrapped indirect effects will be estimated, as well as their 95% CIs based on 10,000 bootstrapped samples, considering a significant mediating effect when the 95% CI of the indirect effect does not include zero.

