**Methods:**

This study protocol presents a single-blind randomized controlled trial (RCT) that encompasses baseline, post-treatment, and six-month follow-up assessment time points. A total of 100 patients diagnosed with Long COVID by the Spanish National Health Service will be randomly assigned to either AIR + Mindfulness (n = 50) or relaxation intervention (n = 50), the latter as a control group. The primary outcome will be quality of life assessed using the Short Form-36 Health Survey (SF-36). Additional outcomes such as fatigue, pain, anxiety, memory, and sleep quality will also be evaluated. Mixed effects regression models will be used to estimate the effectiveness of the program, and effect size calculations will be made.

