### Sample size

According to a previous study, when use of the AIR + Mindfulness intervention was compared to a similar active control group (i.e., relaxation therapy) on a sample of fibromyalgia patients, it demonstrated an overall improvement in the severity of the disorder––measured using the Fibromyalgia Impact Questionnaire Revised [32], a tool that evaluates the effect of this condition on a person’s wellbeing and quality of life, considering pain levels, physical functioning, sleep quality, fatigue, mood, and the impact of the condition on daily activities––with a moderate effect size (d = 0.60) at post-intervention [22]. Assuming a similar effect size in terms of quality of life on Long COVID symptomatology at post-intervention, in order to detect this difference with an overall α level of 5% and a statistical power set at 80% in two-tailed tests, 42 patients per group are required. Given that a dropout rate of around 15% of the participants is expected [33], the sample size will be increased until the number of 50 participants is achieved per group at the beginning of the study.

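### The primary SF-36 test does not name baseline SF-36 as a covariate or set a common baseline mean; on its ordinary reading it compares mean changes and gives up efficiency that baseline adjustment would recover at no cost

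*Protocol article*

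**What the plan says.** The Data analysis plan section makes the primary analysis a comparison of the two arms at post-intervention on SF-36, by intention to treat, in a repeated-measures design. The model is "a linear mixed effects regression by means of the restricted maximum likelihood (RML) method, controlling for age and sex". The tested term is the treatment-by-time interaction: this "interaction will be calculated to determine possible differences between the study arms over time". The estimate is "The slope coefficient, representing the adjusted mean difference change", reported with a 95% CI. Hedges' g, "as an effect size measure of between-group differences, will be calculated from the raw data", is reported as well. The three-month effect and the secondary outcomes follow the same approach as secondary analyses.

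Table 3 lists SF-36 at baseline, post-treatment and three-month follow-up. The Randomization, allocation, and blinding section places allocation after the baseline surveys are complete.

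The Sample size section takes an effect from an earlier fibromyalgia trial, "with a moderate effect size (d = 0.60) at post-intervention", and states that "with an overall α level of 5% and a statistical power set at 80% in two-tailed tests, 42 patients per group are required". It adds that "a dropout rate of around 15% of the participants is expected" and raises the number to 50 per group. It mentions neither a pre-post correlation nor baseline adjustment.

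**The concern.** Age and sex are the only covariates named. When baseline is one of the repeated outcomes and each arm has its own baseline mean, the treatment-by-time term at post-intervention is the difference between arms in mean change. Main effects of age and sex are constant within a person, so they do nothing to sharpen that within-person contrast.

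Because everyone is measured before allocation, the arms have equal expected baseline means. An analysis that uses this fact, through a baseline covariate or a common baseline mean, has a smaller variance at every ρ below 1. Precision on the one confirmatory test is at stake. The trial was also sized on a difference in post-intervention scores, so the planned change contrast could have more or less power than the stated 80%, depending on a correlation that is not given.

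**Working it through.** **Inputs.** From the Sample size section: d = 0.60 (so SD = 1), two-sided α = 0.05, power 80%, 42 per group, 15% dropout, 50 per group randomised. Assumed: equal SDs at baseline and post-intervention, and a pre-post correlation ρ. The article gives no ρ, so a range is shown.

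**The plan's own figure.** Normal approximation: n = 2 × ((1.96 + 0.842)/0.60)² = 43.6, so 44 per group. Power at 42 per group is 78.5%. The exact t-test needs 45 and gives 77.6% at 42. The stated 42 is thus reproduced to within two patients on the normal approximation. For dropout, 42/0.85 = 49.4, which rounds up to 50, as stated.

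**Variances per person, in units of SD².**
- Post-score comparison (the basis of the sizing): 1
- Difference in mean changes: 2(1 − ρ)
- Baseline-adjusted: 1 − ρ²

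The ratio of adjusted to change variance is (1 − ρ²)/(2(1 − ρ)) = (1 + ρ)/2, so the information lost by the change contrast is 1 − (1 + ρ)/2 = (1 − ρ)/2.

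**Power** at 42 per group is Φ(0.60/√(2V/42) − 1.96), with V the variance above. Example at ρ = 0.3: V = 1.40 gives a standard error of 0.258 and power of 64.2%; V = 0.91 gives 0.208 and 82.2%.

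| ρ (assumed) | V, change | V, adjusted | Information lost | Power, change | Power, adjusted | n per group for 80%: change / adjusted |
|---|---|---|---|---|---|---|
| 0.2 | 1.60 | 0.96 | 40% | 58.5% | 80.1% | 70 / 42 |
| 0.3 | 1.40 | 0.91 | 35% | 64.2% | 82.2% | 62 / 40 |
| 0.4 | 1.20 | 0.84 | 30% | 70.9% | 85.1% | 53 / 37 |
| 0.5 | 1.00 | 0.75 | 25% | 78.5% | 88.8% | 44 / 33 |
| 0.6 | 0.80 | 0.64 | 20% | 86.7% | 93.0% | 35 / 28 |
| 0.7 | 0.60 | 0.51 | 15% | 94.4% | 97.1% | 27 / 23 |
| 0.8 | 0.40 | 0.36 | 10% | 99.2% | 99.6% | 18 / 16 |
| 0.9 | 0.20 | 0.19 | 5% | >99.9% | >99.9% | 9 / 9 |

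**Comparison with the sizing.** The change contrast has a larger variance than the post-score comparison when 2(1 − ρ) > 1, that is, when ρ < 0.5. At ρ = 0.5 the two are equal (78.5%); above it the change contrast is the stronger. The adjusted analysis is at least as good as both throughout.

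**Effect of dropout.** A mixed model keeps people who give only a baseline score, so with dropout it is not exactly a change-score test. Generalised least squares was used for three waves with compound symmetry, 50 per arm and 15% in each arm with baseline only. It compared free with common baseline means:

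| ρ | Variance, free baselines | Variance, common baseline | Information lost |
|---|---|---|---|
| 0.3 | 0.0624 | 0.0428 | 31% |
| 0.5 | 0.0453 | 0.0353 | 22% |
| 0.7 | 0.0276 | 0.0240 | 13% |

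The loss is slightly smaller than with complete data, and the pattern is the same.

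**The case against.** The strongest reply is that free baseline means are inferred. The article never says that the arms have separate baseline means, and its wording could be fitted with a common one, which would recover the efficiency. The Data Availability section refers to a statistical analysis plan that is not shown. This stands as a caution. Even so, the article does fix the covariates, the tested term and the meaning of the coefficient, and a change contrast is what those three ordinarily describe.

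It is also fair that the loss depends on ρ. The only retest correlations in the article are 0.84 for the Pain Catastrophizing Scale and 0.79 for the Acceptance and Action Questionnaire-II. They concern other instruments and do not settle the SF-36 value, but nothing in the article points to a low ρ either. At ρ = 0.7 the gain in power is under three points.

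A reader might infer more than the article supports:
- **A fixed loss of 15–35%.** This holds only if ρ lies between 0.3 and 0.7.
- **Bias or an inflated type I error.** Neither follows. Under randomisation the change contrast is valid.
- **A linear trend over three waves in place of the post-intervention difference.** The word slope invites this. But the same section puts the primary comparison at post-intervention, counts a single contrast, and makes the three-month effect secondary. Slope there reads as a regression coefficient.
- **A Hedges' g restricted to completers, or distorted by baseline imbalance to a known degree.** The article says only that g comes from raw data. It does not say whose data, or whether post scores or changes are used, so no size can be attached.

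**Conclusion.** The point holds as a matter of efficiency, not validity. On the ordinary reading, the primary test forgoes (1 − ρ)/2 of the available information: 35%, 25% and 15% at assumed ρ of 0.3, 0.5 and 0.7, and 40% down to 5% across ρ from 0.2 to 0.9. The practical consequence is considerable if ρ is low and small if it is high. These figures rest on equal SDs at the two visits, d = 0.60 on the post-score SD, and baseline means left free. If the full analysis plan already imposes a common baseline mean, the loss disappears and only the wording needs to be made explicit.

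The raw-data g is unadjusted and so need not match the age- and sex-adjusted model estimate. It drives no test, so this is a reporting matter.

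**What to change.** Keep the single contrast between arms at post-intervention. State that it is estimated in one of two ways: with baseline SF-36 as a covariate, or in the mixed model with categorical time and a common baseline mean across arms. Apply the same rule to each secondary outcome with its own baseline. Optionally, report a standardised effect derived from the adjusted estimate beside the raw-data Hedges' g.

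The cost is a change of analysis wording, to be made before unblinding. Baseline is already collected before allocation, so no new data, visits or participants are needed.

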### Objectives and hypotheses

The primary aim of the study proposed in this protocol is to evaluate the impact of the AIR + Mindfulness on enhancing the quality of life of patients with Long COVID. The secondary objectives include (a) to examine the effects of AIR + Mindfulness on pain, pain catastrophizing, fatigue, insomnia, anxiety, depression, and memory symptoms; and (b) to analyze the role of mindfulness skills, emotion regulation, and experiential avoidance as potential mechanisms through which AIR + Mindfulness exerts its effects.

The main hypothesis is that AIR + Mindfulness will be more effective than relaxation therapy for improving quality of life among patients diagnosed with Long COVID at post-treatment. The secondary hypotheses are (a) AIR + Mindfulness will be more effective than relaxation therapy for improving pain, pain catastrophizing, fatigue, insomnia, anxiety, depression, and memory symptoms at post-treatment; (b) improvements in all psychological variables will be sustained at the three-month follow-up; and (c) mindfulness skills, emotion regulation, and experiential avoidance will play a mediating role in the improvement observed in the AIR + Mindfulness experimental group compared to the relaxation therapy control group.

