### Outcomes

Data will be collected using a battery of self-reported questionnaires administered at baseline, after the intervention (post-intervention,) and at three-month follow-up. Outcomes of the AIR + Mindfulness and the relaxation conditions will be evaluated and compared. All variables and assessment periods of the study can be found in Table 3.

**Table 3 Tab3:** Study Outcomes

Instrument	Assessment Area	Time
Bespoke survey	Sociodemographic	Baseline
SF-36	Quality of life	Baseline, post-treatment and 3-month follow-up
SCPGS	Pain intensity	Baseline, post-treatment and 3-month follow-up
PCS	Catastrophizing	Baseline, post-treatment and 3-month follow-up
MFIS	Fatigue	Baseline, post-treatment and 3-month follow-up
ISI	Insomnia	Baseline, post-treatment and 3-month follow-up
GAD-7	Anxiety	Baseline, post-treatment and 3-month follow-up
PHQ-9	Depression	Baseline, post-treatment and 3-month follow-up
MEF-30	Memory	Baseline, post-treatment and 3-month follow-up
FFMQ-24	Mindfulness	Baseline, post-treatment and 3-month follow-up
ERQ	Emotion Regulation	Baseline, post-treatment and 3-month follow-up
AAQ-II	Experiential avoidance	Baseline, post-treatment and 3-month follow-up

SF-36, Short Form Health Survey; SCPGS, Spanish Chronic Pain Grading Scale; PCS, Pain Catastrophizing Scale; MFIS, Modified Fatigue Impact Scale; ISI, Insomnia Severity Index; GAD-7, General Anxiety Disorder; PHQ-9, Patient Health Questionnaire; MEF-30, Memory Failures of Everyday; FFMQ-24, Five Facet Mindfulness Questionnaire; ERQ, Emotion Regulation Questionnaire; AAQ-II, Acceptance and Action Questionnaire-II.

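### As published, the mediation analysis rests on change scores with no baseline covariate named; this costs precision and can produce a mediated effect that is not there

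*Protocol article*

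**What the plan says.** Secondary hypothesis (c), under Objectives and hypotheses, is that "mindfulness skills, emotion regulation, and experiential avoidance will play a mediating role in the improvement observed" in the intervention arm. The Data analysis plan then builds the model in three lettered items:

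- Dependent variable: "pre-follow-up differential scores for primary and secondary outcomes will be considered dependent variables".
- Mediators: "pre-post differential scores for mindfulness skills, emotion regulation, and experiential avoidance will be calculated and included as process variables".
- Independent variable: "the group condition (AIR + Mindfulness vs. relaxation therapy) will be considered the independent variable".

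On estimation, "The mediating analyses will be conducted using ordinary least squares (OLS) regression and path analysis", with 10,000 bootstrap samples and a decision rule: "considering a significant mediating effect when the 95% CI of the indirect effect does not include zero".

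No covariate is listed for these regressions. The primary mixed model in the same section does list its covariates ("controlling for age and sex"). The Outcomes section and its Table 3 show that every outcome and every mediator comes from "self-reported questionnaires administered at baseline, after the intervention (post-intervention,) and at three-month follow-up", so all the baseline values will be in hand.

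**The concern.** Both differences subtract a score taken at the same baseline sitting. The instruments differ, but a participant having a bad day may score worse on mediator and outcome together. That shared deviation is then subtracted from both later scores, and the two changes move together even if the mediator does nothing. Randomisation keeps the group-to-mediator path free of bias, but it does not protect the mediator-to-outcome path.

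Baseline noise also makes the group-to-mediator path less precise than the data allow. The conclusion on mechanism rests on whether one confidence interval excludes zero, for several mediators and for the primary and secondary outcomes. That rule could report a mechanism that is not operating or, under some mechanisms, miss one that is.

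**Working it through.** **Inputs from the article.** 42 per group after dropout, two-sided 5%, effect 0.60 SD (Sample size); AAQ-II test-retest r = 0.79 (Mechanistic measures), used as an upper anchor for the baseline-to-later correlation. The article gives no figure for the mediation analysis itself. As a check on the 42: 2(1.96 + 0.84)²/0.6² = 43.6, so 44, close to the stated 42; and 42/0.85 = 49.4, so 50. This input is not in dispute.

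**Assumptions, not in the article.** Other values of r; the baseline mediator-outcome correlation ρ; an effect of 0.6 SD on the mediator.

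**1. Precision of the group-to-mediator path.** With unit variances, a change score has variance 2(1−r). After adjustment for its own baseline the variance is 1−r² = (1−r)(1+r). The ratio is 2/(1+r).

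- r = 0.5: 2/1.5 = 1.33. Power for 0.6 SD with 42 per arm: 78.5% against 88.8%.
- r = 0.7: 2/1.7 = 1.18.
- r = 0.79: 2/1.79 = 1.12. Power: 98.9% against 99.4%.

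**2. Spurious path when each baseline carries forward only into its own later score.** Suppose the mediator has no effect. Within a group the two changes have covariance ρ(1−r)², and the mediator change has variance 2(1−r). The regression slope is therefore ρ(1−r)/2. Simulation used 84 analysed and 2,000 trials per setting, with a Monte Carlo interval for the product standing in for the bootstrap:

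| r | slope at ρ = 0.6 | false mediation at ρ = ±0.6, change scores | same, both baselines added |
|---|---|---|---|
| 0.4 | 0.6 × 0.6/2 = 0.18 | 20–25% | 4.2–4.4% |
| 0.5 | 0.6 × 0.5/2 = 0.15 | 19–21% | 4.4–4.7% |
| 0.6 | 0.6 × 0.4/2 = 0.12 | 16–19% | 4.6–6.4% |
| 0.79 | 0.6 × 0.21/2 = 0.063 | 8–9% | 4.0–6.2% |

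At ρ = ±0.4 the change-score rate is 6–12%. At ρ = 0 there is no bias; the simulated rates there were 3.8–7.9%, which shows the simulation noise and means that the 8–9% at r = 0.79 is a small excess at most.

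**3. Spurious path when each score is a stable trait plus an occasion-specific state.** Let the trait share be λ for both variables and let the same-day state correlation be s. The traits cancel in the differences. The covariance of the changes is (1−λ)s and the variance is 2(1−λ), so the slope is s/2: 0.30 at s = 0.6, twice the value in step 2 at r = 0.5. Simulations with 42 per arm, trait share 0.4–0.7 and trait correlation 0.3–0.6, run several times, gave with no true path:

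- s = 0.6: false mediation 40–78% with change scores, 7–61% with baselines added.
- s = 0.4: 32–42% against 15–30%.
- s = 0 to 0.3 with strong trait correlation: 3–25% against 13–33%.
- s = 0 with strong trait correlation: 3–5% against 10–13%.

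A single baseline score captures a stable trait imperfectly, so conditioning on it leaves some trait confounding that differencing removes. In step 2 there is no such trait, which is why adjustment looks near-perfect there.

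**4. Power to detect a real path.** If the post-treatment mediator level, including its occasion-specific part, drives the outcome (true path 0.3, s = 0), the change-score slope averages about 0.15, and detection is 16–25% against 61–92% adjusted. If true mediator change drives outcome change and the traits are uncorrelated, detection is 6% against 11% in one setting and 20% against 24% in another. The large gap belongs to the first mechanism only.

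**The case against.** The strongest objection is that the absence of baseline adjustment is read from a list. The article does not say in words that baselines are excluded. It is a condensed account, and its Data Availability statement mentions a separate statistical analysis plan that is not shown. A change score regressed on group and its own baseline gives the same group coefficient as the follow-up score so adjusted, so defining the variables as differences does not rule the covariates out. This stands as a limit on wording: a reader might infer that the plan forbids baseline adjustment, and the text does not support that. It does not dispose of the point. The article fixes the variables, estimator, number of bootstrap samples and decision rule, and it names covariates for the primary model in the same section. Someone following it as written would fit change scores alone.

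The second objection is that differencing has a merit of its own, because it removes stable-trait confounding. That stands too, and it is why the change-score model should be kept as a sensitivity analysis. A reader might infer that baseline adjustment is uniformly better or restores the nominal error rate; step 3 shows that it does neither.

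Third, the article documents no mediator-outcome correlation, and at its only stability figure (0.79) the precision loss is small, as is the bias in step 2. That is fair, although a test-retest value is likely to exceed the correlation across an eight-week intervention.

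Finally, the article describes the mediation work as exploratory. It is nevertheless a stated hypothesis with a significance rule.

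**Conclusion.** The point holds for the specification as published. The loss of precision in the group-to-mediator path is certain in direction: 33% more variance at an assumed r = 0.5, falling to 12% at 0.79. The bias in the mediator-to-outcome path is conditional. It needs same-occasion correlation between mediator and outcome at baseline, and its size runs from negligible to severe across the assumed correlations.

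A reader might infer that the plan will miss most real mediation. The documents do not support that as a general statement, because the result turns on whether mediator level or mediator change drives the outcome, and the article does not settle this. Nor is the primary comparison touched: it uses a separate mixed model, and randomisation protects the group-to-mediator path from bias. The consequence is confined to secondary objective (b) and hypothesis (c).

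**What to change.** State the covariates of the mediation model. In both the mediator equation and the outcome equation, include baseline mediator and baseline outcome, together with age and sex as in the primary model, and keep the bootstrap and its interval. Report the unadjusted change-score model as a prespecified sensitivity analysis, and treat disagreement between the two as a sign that the result depends on the assumed form of confounding. Describe the mediator-outcome path as observational in the plan and in the report.

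The cost is two degrees of freedom per equation for the baselines and two for age and sex. With 84 analysed, the residual degrees of freedom in the outcome equation go from 84 − 3 = 81 to 77. There is one extra run, and no new patients, visits or questionnaires. The remaining downside is that adjustment leaves some stable-trait confounding and can give more false mediation than change scores when that is the only confounding present.
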